## **5.1 recording and reporting**

Care will be taken not to introduce bias when detecting AEs and/or SAEs. Open-ended and non-leading verbal questioning of the subject is the preferred method to inquire about AE occurrence. Regardless the relevance to the medicine, A it is the responsibility of the investigator to review all documentation (e.g., hospital progress notes, laboratory, and diagnostics reports) relative to the event. The investigator will then record all relevant information regarding an AE/SAE in the appropriate data collection tool.

The investigator will attempt to establish a diagnosis of the event based on signs, symptoms, and/or other clinical information. In such cases, the diagnosis will be documented as the AE/SAE and not the individual signs/symptoms.

If any patient suffers an event that fulfils these criteria, a Serious Adverse Event Form should be completed and faxed to the Principal Investigator **within 24 hours of the event being known.** The original form should be stored in the Investigator File and a copy placed in the patient’s source notes.

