# Patient

## **2.1 Diagnostic criteria**

### 2.1.1 Alzheimer’s disease

According to the Diagnostic criteria for 294.1x Dementia of the Alzheimer's type in Diagnostic and Statistical Manual of Mental Disorders, 4th edition (DSM-IV) (APA, 1994)：

A. The development of multiple cognitive deficits manifested by both

(1) memory impairment (impaired ability to learn new information or to recall previously learned information)

(2) one (or more) of the following cognitive disturbances

(a) aphasia (language disturbance)

(b) apraxia (impaired ability to carry out motor activities despite intact motor function)

(c) agnosia (failure to recognize or identify objects despite intact sensory function)

(d) disturbance in executive functioning (i.e., planning, organizing, sequencing, abstracting )

B. The cognitive deficits in Criteria A1 and A2 each cause significant impairment in social or occupational functioning and represent a significant decline froma previous level of functioning.

C. The course is characterized by gradual onset and continuing cognitive decline.

D. The cognitive deficit in Criteria A1 and A2 are not due to any of the following:

(1) other central nervous system conditions that cause progressive deficits in memory and cognition( e.g., cerebrovascular disease, Parkinsin's disease, Huntington's disease, subdural hematoma, normal-pressure hydrocephalus, brain tumor)

(2) systemic conditions that are known to cause dementia (e.g., hypothyroidism, vitamin B_12_ or folic acid deficieney, niacin deficiency, hypercalcemia, neurosyphilis, HIV infection)

(3) substance-induced conditions

E.The deficits do not occur exclusively during the course of delirium.

F. The disturbance is not better accounted for by another Axis I disorder(e.g., Major Depressive Disorder, Schizophrenia).

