## **2.2 Inclusion criteria**

(1) a diagnosis of dementia of the Alzheimer’s type according to the Diagnostic and Statistical Manual of Mental Disorders, 4th edition (DSM-IV) (APA, 1994);

2) a diagnosis of Syndrome of kidney and marrow deficiency

(3) women or men aged 50–85 years;

(4) Hachinski Ischemic Score(HIS) ≤4;

(5) Hamilton Anxiety Scale(HAMD) score of ≤7;

(6)Written informed consent from all patients (or their legal representatives);

(7) Clinical Dementia Rating (CDR) score of 1.

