## **3.5 Time point**

(1) Cognitive scales: baseline (0 week), week 12(treatment), week 24(treatment), week -48(follow up);

(2) Imaging (BOLD-fMRI, magnetic resonance spectroscopy, hippocampus formation): baseline (0 week), week 12(treatment);

(3) NEI network: baseline (0 week), week 4(treatment), week 24(treatment);

(4) Safety outcomes: baseline (0 week), week 12(treatment), week 24(treatment)**;**

(5) Specific parameters related to AD: baseline (0 week), week 12(treatment).

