# Auxiliary examination

## **4.1 Dynamic outcomes**

### 4.1.1 Detection outcomes

（1）安全性指标：血、尿、便常规，心电图，ALT、AST、BUN、Cr

(1) safety outcomes: blood, urine, stool routine, electrocardiogram, ALT, AST, BUN, Cr（2）疗效性指标：NEI网络指标（促肾上腺皮质激素、血浆皮质醇、生长激素、雌二醇、睾酮、儿茶酚胺、乙酰胆碱、血管活性肠肽、促甲状腺素；CD3+、CD4+、CD8+细胞比例，CD4+/CD8+之比；IL-2、IFNγ、TGF、IL-1），T-tau、P-tau、Aβ1-42

(2) outcomes of curative effect: NEI network index (adrenocorticotropic hormone, cortisol, growth hormone, estradiol, testosterone, catecholamine, acetylcholine, vasoactive intestinal peptide, thyroid stimulating hormone; CD3+, CD4+, CD8+ , CD4+/CD8+ ; IL-2, IFNγ, TGF, IL-1), T-tau, P-tau,Aβ1-42

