## **6.2 Compliance**

In order to ensure the compliance of the participants, the participants should be made to fully understand the significance of this study and the importance of taking medicine on time.

(1) The participants should be asked to take medicine on time by caregivers.

(2) The drugs should be counted and the patients should return the remaining drug at follow up. Researchers should count the number of drugs, record the detailed reasons for incompletely intake, and strengthen the monitoring of poor efficacy or poor compliance of the patients.

(3) Compliance evaluation: compliance = (the actual dose / planed dose) *100%

good compliance: 80%-120% compliance

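### Adverse events are to be sought by open-ended questioning of patients who all have memory impairment, and the caregiver is given no part in detection

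*Protocol*

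**What the plan says.** Section 5.1 sets the method: "Open-ended and non-leading verbal questioning of the subject is the preferred method to inquire about AE occurrence". This is the only way of asking about adverse events that the protocol states. The rest of section 5.1 covers review of documentation, diagnosis and SAE forms, and section 5.2 covers follow-up. No caregiver or other informant appears anywhere in section 5.

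The population is fixed in section 2.2, which requires "a diagnosis of dementia of the Alzheimer’s type according to the Diagnostic and Statistical Manual of Mental Disorders, 4th edition (DSM-IV) (APA, 1994") and a "Clinical Dementia Rating (CDR) score of 1". Section 2.1.1 reproduces the diagnostic criteria. Criterion A(1), which must be met together with A(2), is "memory impairment (impaired ability to learn new information or to recall previously learned information").

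Caregivers enter the protocol in section 6.2, for drug intake: "The participants should be asked to take medicine on time by caregivers".

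On timing, section 3.5 gives "Safety outcomes: baseline (0 week), week 12(treatment), week 24(treatment"). Section 4.1.1 defines what these are: "1) safety outcomes: blood, urine, stool routine, electrocardiogram, ALT, AST, BUN, Cr". Section 5.1 gives no schedule for adverse event questioning.

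**The concern.** Open, non-leading questions protect against suggestion and are worth keeping. The difficulty is the person to whom they are put. An open question gives no cue, so the answer rests on the patient's own recall, and impaired recall is part of the entry diagnosis. The protocol allows for this limitation elsewhere: legal representatives may consent (section 2.2) and caregivers prompt medication (section 6.2). Only for adverse events is the patient the sole named informant.

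What is at stake is the completeness of the symptomatic safety record. A brief symptom that resolves without a test, a consultation or an admission leaves nothing to find later. If the patient does not report it, it cannot be recovered at analysis.

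**Working it through.** The protocol states no adverse event rate, detection rate or power for safety, so there is no figure to reproduce. The check is first of the text, then an illustration on assumed rates.

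**Text**

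1. *Is memory impairment universal?* Yes. Section 2.2 requires the diagnosis of every patient, and criterion A(1) is compulsory within it.
2. *Is another informant named?* No. The caregiver's stated task is medication (section 6.2).
3. *Would other provisions catch a missed event?*
   - Record review in section 5.1 concerns documents relating to an event, and section 5.2 begins after a first report. Both presuppose a known event.
   - Laboratory tests and ECG (section 4.1.1) do not depend on recall, and hospitalisations leave notes. These kinds of event are much less affected.
   - What remains exposed is the transient symptomatic event with no record.
4. *When are patients asked?* Not stated. The safety time points at weeks 0, 12 and 24 are for laboratory tests and ECG. Section 3.5 also lists a week-4 contact for NEI sampling and a week-48 follow-up for cognitive scales. The intervals between dated contacts are therefore 4, 8, 12 and 24 weeks (0 to 4, 4 to 12, 12 to 24, 24 to 48). Drug distributions and returns (sections 3.6.2 and 6.2) add contacts whose frequency is not given.

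**Illustration**

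Inputs: 40 + 20 + 60 = 120 patients at 1:1 (section 3.2), so n = 60 per arm. Assumed, not in the protocol: the true event rates, two-sided alpha of 0.05, and s, the share of events reported, taken as equal in both arms.

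(a) *Chance of at least one report in an arm*, true rate 5%: 1 − (1 − 0.05s)^60.

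| s | reported rate | chance of at least one report |
|---|---|---|
| 1.0 | 0.05 | 1 − 0.95^60 = 0.954 |
| 0.8 | 0.04 | 1 − 0.96^60 = 0.914 |
| 0.6 | 0.03 | 1 − 0.97^60 = 0.839 |
| 0.4 | 0.02 | 1 − 0.98^60 = 0.702 |

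(b) *Power to see true rates of 30% against 10%.* With p1 = 0.30s, p2 = 0.10s and p the mean of the two, power = Φ{[(p1 − p2) − 1.96·√(2p(1 − p)/60)] / √[(p1(1 − p1) + p2(1 − p2))/60]}.

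| s | expected counts | difference | power |
|---|---|---|---|
| 1.0 | 18 v 6 | 20 points | 0.789 |
| 0.8 | 14.4 v 4.8 | 16 points | 0.670 |
| 0.6 | 10.8 v 3.6 | 12 points | 0.525 |
| 0.4 | 7.2 v 2.4 | 8 points | 0.364 |

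The risk ratio is 3 in every row. Equal under-reporting leaves it unchanged and reduces the absolute difference and the power.

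**The case against.** **Preferred does not mean exclusive.** Nothing in section 5.1 stops a caregiver volunteering an event or an investigator asking one. The disease is mild (CDR 1), and section 2.3 excludes aphasia and severe hearing loss, so many patients can describe symptoms. This stands, and it makes the loss a risk rather than a certainty. It does not remove the point: the stated method is the only one given, and a site that never asks a caregiver complies fully.

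**The size is assumed.** This stands. No event or recall rate can be taken from the protocol, and the tables above show only how a given loss would act.

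**Caregivers are not guaranteed.** Section 2.2 does not require one, and section 6.2 does not ask caregivers to attend visits. This stands, and any remedy must allow for patients without one.

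Two stronger readings are tempting, and neither is supported.

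- *Patients must recall 12 weeks of symptoms.* A reader might infer this from the safety time points in section 3.5. Those time points govern laboratory tests and ECG, a week-4 contact exists, and drug returns may fall in between. The text establishes only that the times of questioning are unstated.
- *The safety comparison is confounded by efficacy*, because the arm with better cognition would report more. This needs a between-arm cognitive difference large enough to shift recall, and the protocol gives no basis for one. Even with an assumed 50% against 60% recall of 18 events per arm, the expected counts are 9 and 10.8. That is 15% against 18%, a gap of 3 points with a standard error of √[(0.15 × 0.85 + 0.18 × 0.82)/60], about 6.8 points.

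**Conclusion.** The point holds as a weakness in a stated method. The protocol prefers, and names only, the informant whose memory is impaired by definition, and it leaves out the caregiver on whom it already relies for medication. The likely consequence is under-recording of transient symptomatic events that leave no trace.

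The text is certain and the size of the loss is not. On the assumed rates, if 40% to 80% of events are reported, the chance of seeing a 5% event at least once in an arm is 0.70 to 0.91, against 0.95 with full reporting. With 60 patients per arm there is little room for lost reports. The point does not touch the efficacy analysis and does not show bias in favour of either arm. The change is worth making because it is cheap and unrecorded events cannot be recovered later.

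**What to change.** In section 5.1, keep the open-ended, non-leading style and replace the sentence on method with wording such as:

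> AEs are elicited by open-ended, non-leading questions put to the patient and, where one is available in person or by telephone, to the caregiver, at each existing study contact: weeks 4, 12 and 24, the week-48 follow-up, and drug returns. An event reported by either is recorded, and the informant is noted in the CRF. Where no caregiver is available, the patient alone is asked and this is noted.

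This also supplies the missing times of questioning without adding visits.

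The cost is a wording change, one CRF field for the informant, a few more minutes per visit and some telephone calls. Recorded event counts will probably be somewhat higher, and a reader should not take that as greater harm. Patients without an available caregiver will still have patient-only reporting. The informant field lets the report show how many they are.

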## **5.2 Follow up of AEs**

After the initial AE/SAE report, the investigator is required to proactively follow each subject at subsequent visits/contacts. All AEs and SAEs will be followed until resolution, until the condition stabilizes, until the event is otherwise explained, or until the subject is lost to follow-up.

The investigator is obligated to perform or arrange for the conduct of supplemental measurements and/or evaluations as may be indicated or as requested to elucidate as fully as possible the nature and/or causality of the AE or SAE. The investigator is obligated to assist. This may include additional laboratory tests or investigations, histopathological examinations or consultation with other health care professionals.

# 6 Quality assurance

## **6.1 Investigators**

(1) The researchers should be relatively permanent, and with clinical research expertise, qualification and ability.

(2) Before the trial, investigators should learn the study protocol carefully and make sure all the various technical indicators.

(3) Participants should be followed up in accordance with the protocol; if the patients fail to return on time, the physicians should inform the referral or to follow up.

## **6.2 Compliance**

In order to ensure the compliance of the participants, the participants should be made to fully understand the significance of this study and the importance of taking medicine on time.

(1) The participants should be asked to take medicine on time by caregivers.

(2) The drugs should be counted and the patients should return the remaining drug at follow up. Researchers should count the number of drugs, record the detailed reasons for incompletely intake, and strengthen the monitoring of poor efficacy or poor compliance of the patients.

(3) Compliance evaluation: compliance = (the actual dose / planed dose) *100%

good compliance: 80%-120% compliance

## **6.3 Laboratory test**

(1) Safety outcomes should be performed in accordance with the standard operation of clinical test in each center.

(2)NEI network and specific protein test should follow the instructions by Longhua hospital.

## **6.4 Muti-center coordinating committee**

The sponsor should be in charge of building clinical coordinating committee in every center. The committees function in coordinating the trial and solve problems.

## **6.5 Monitors**

The sponsors can send monitors to ensure the trial.

# 7 Data management

## **7.1 Case report form (CRF)**

The investigators should copy and fax pp. 7-8 of the CRF (the general data, history, etc) to the Second Affiliated Hospital of Tianjin University of Traditional Chinese Medicine three days after the enrichment, in order to guarantee timely information summary analysis. Fax number: [name].

According to the original observation records of the patients, the investigators should record the date timely, correctly, completely, and clearly. CRF should be completed in three days after the patients leave. The completed CRF should also be transferred to the data administrator after checked by the monitors.

## **7.2 Data entry and modification**

Data manager is responsible for data entry and management. The dada manager defines the data range checking and logic checking content with the main researchers, according to the range of values of each index of CRF, and write program. Before inputting, control error data, and record all error content and modified results. In order to ensure th integrity of data, the data should be input by two independent data administrator.

## **7.3 Data processing**

After confirming the corrective of the database established, research administrators and statistical analysis should lock the data. The errors found after locking should be modified by the statistical analysis program after confirming the error. The database should be analyzed by the statistician, and the statistician report he data analysis to the sponsors to finish a study report.

# 8 Confidentiality

The clinical researcher should pay attention to the secrecy of the trial, and should not leak the data to others.
